#### Secondary outcome

Secondary outcomes will be as follows:
OS is defined as the time from initiation of study treatment to death due to any causeDCR is defined as the percentage of patients whose best response was not progressive disease (i.e., complete response, partial response or stable disease)Time to progression is defined as the time (in days) from the start of study treatment to the first documented disease progressionDuration of treatment is defined as the time interval from the start of study treatment to the day of permanent discontinuation (including death); mean dose and reasons for treatment discontinuation or dose modification will be recorded

### Safety assessment

The treatment-associated AEs will be assessed and recorded in each cycle using Common Terminology Criteria for Adverse Events version 5.0.

### Safety stopping rules

The study will be stopped according to the will or condition of the patients as judged by the investigators, or if any grade 4 AE develops.

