##### Subgroup 1: UGT1A1*1/*1 genotype

Oral regorafenib will be administered at a dose of 120 mg once daily for the first 3 weeks of each 4-week cycle. A FOLFIRI regimen will be initiated at a dose of 180 mg/m^2^ irinotecan and 200 mg/m^2^ LV intravenous (IV) infusion over 2 h followed by 5-FU (2800 mg/m^2^ as an IV infusion over a 46-h period). If no FOLFIRI-related AEs greater than grade 3 are observed after two cycles of each dose of irinotecan, the dose of irinotecan will be escalated in steps of 30 mg/m^2^. If any FOLFIRI-related AEs greater than grade 3 are encountered, the dose of irinotecan will be reduced by 30 mg/m^2^ or back to the previous dose and be held at that dose at the next cycle. The maximum dose of irinotecan for subgroup 1 is 260 mg/m^2^.

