##### Subgroup 2: UGT1A1*1/*28 genotype

Oral regorafenib will be administered at a dose of 120 mg once daily for the first 3 weeks of each 4-week cycle. A FOLFIRI regimen will be initiated at a dose of 180 mg/m^2^ irinotecan and 200 mg/m^2^ LV IV infusion over 2 h followed by 5-FU (2800 mg/m^2^ as an IV infusion over a 46-h period). If no FOLFIRI-related AEs greater than grade 3 are observed after two cycles of each dose of irinotecan, the dose of irinotecan will be escalated in steps of 30 mg/m^2^. If any FOLFIRI-related AEs greater than grade 3 are encountered, the dose of irinotecan will be reduced by 30 mg/m^2^ or back to the previous dose and be held at that dose at the next cycle. The maximal dose of irinotecan for subgroup 2 is 240 mg/m^2^.

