##### Subgroup 3: UGT1A1*28/*28 genotype

Oral regorafenib will be administered at a dose of 120 mg once daily for the first 3 weeks of each 4-week cycle. A FOLFIRI regimen will be initiated at a dose of 120 mg/m^2^ irinotecan and 200 mg/m^2^ LV IV infusion over 2 h followed by 5-FU (2800 mg/m^2^ as an IV infusion over a 46-h period). If no FOLFIRI-related AEs greater than grade 3 are observed after two cycles of each dose of irinotecan, the dose of irinotecan will be escalated in steps of 30 mg/m^2^. If any FOLFIRI-related AEs greater than grade 3 are encountered, the dose of irinotecan will be reduced by 30 mg/m^2^ or back to the previous dose and be held at that dose at the next cycle. The maximal dose of irinotecan for subgroup 3 is 180 mg/m^2^.

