#### Stopping treatment/other medications

All treatment will be stopped in the event of patient withdrawal, disease progression, or unacceptable AEs, which are defined as nonhematological grade 4 AEs, no recovery from grade 3 AEs after two consecutive dose reductions, or no recovery after a 2-week treatment delay.

Throughout the study period, participants should not receive other cytotoxic or biological treatments for mCRC. If concomitant treatments are considered necessary based on investigator discretion, the product package insert should be referenced for contraindications and all concomitant treatments should be recorded on the relevant case report form (CRF) page.

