## Discussion

RTKs, such as VEGF receptor, EGFR, fibroblast growth factor receptor, platelet-derived growth factor receptor, RET and KIT, are responsible for several biological signaling pathways involved in the regulation of angiogenesis, oncogenesis and the tumor microenvironment [1]. Regorafenib is a small molecule that binds to and inhibits RTKs and therefore has antineoplastic activities. It is for this reason that regorafenib also shows various AEs, including HFSR, hypertension, thrombocytopenia, proteinuria, diarrhea, mucositis, hepatoxicity and so on. The most frequent grade 3 or higher AE related to regorafenib is HFSR, which results in dose reduction or interruption of treatment [2] and may limit the oncological efficacy of regorafenib. The occurrence of HFSR is even higher in the Asian population [11]. Modification of the dosing schedule (a change from a 160-mg dose given once daily, 21 days on, 7 days off, to 120 mg daily, 28 days on with the same accumulated dose of 3360 mg in a cycle) still has high rates of grade 3 HFSR although this recovers sooner than with the standard dosing schedule [9]. A Japanese study in which a dose reduction from 160 mg to 120 mg for 3 weeks in a 4-week cycle largely decreased the occurrence of grade 3 HFSR (75.0% in the 160-mg group and 16.7% in the 120-mg group) with comparable DCR (60.0% in the 160-mg group and 58.3% in the 120-mg group) [4]. As a result, the dose of regorafenib administered in the present study will be 120 mg once daily for the first 3 weeks in each 4-week cycle.

*UGT1A1* activity is the main factor determining cytotoxicity and AEs of irinotecan, and the US Food and Drug Administration has approved *UGT1A1* genotyping to predict irinotecan-induced severe diarrhea and neutropenia [12]. According to the *UGT1A1* genotype, an optimal dose of irinotecan can be achieved with balanced efficacy and toxicity for individuals. Lu et al. demonstrated a prognostic advantage of irinotecan dose escalation in an observational study on the basis of *UGT1A1* genotyping for mCRC treated with FOLFIRI plus bevacizumab [8], and an ongoing prospective, randomized controlled clinical trial is being conducted to examine the efficacy and safety of the aforementioned treatment [10].

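### The safety stopping rule contradicts the treatment-stopping and dose-reduction rules for hematological grade 4 AEs, and the dose trigger as worded leaves out grade 3

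*Protocol article*

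**What the plan says.** Three sets of rules in the Protocol article govern what happens after a severe AE.

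- **Safety stopping rules.** The study is stopped according to the patients' will or condition, "as judged by the investigators, or if any grade 4 AE develops". There is no limit by organ class or by relation to study drug. The subject of the sentence is the study, and the section does not say whether that means the trial or one patient's participation.
- **Stopping treatment/other medications.** All treatment stops for withdrawal, progression or unacceptable AEs, "which are defined as nonhematological grade 4 AEs, no recovery from grade 3 AEs after two consecutive dose reductions", or failure to recover after a treatment delay of two weeks.
- **Interventions.** In both arms a regorafenib-related AE above grade 3 leads to interruption until recovery and then a 40 mg reduction. In the three genotype subgroups the escalation condition reads "If no FOLFIRI-related AEs greater than grade 3 are observed after two cycles of each dose of irinotecan", after which irinotecan rises by 30 mg/m². The reduction rule reads "If any FOLFIRI-related AEs greater than grade 3 are encountered, the dose of irinotecan will be reduced by" 30 mg/m², or the dose returns to the previous level, and it is kept there at the next cycle. The caps are 260, 240 and 180 mg/m² in subgroups 1, 2 and 3 ("The maximum dose of irinotecan for subgroup 1 is 260 mg"; "The maximal dose of irinotecan for subgroup 2 is 240 mg").

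**The concern.** Two separate faults appear when these sections are read together.

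**Conflicting instructions for grade 4.** The treatment-stopping section confines its grade-based stop to nonhematological events, so hematological grade 4 is left to the dose rules. The safety stopping rule has no such limit. Centres that follow different sections would handle the same patient differently. This bears on safety and on the secondary endpoint duration of treatment, which ends at permanent discontinuation. If the rule is meant at trial level, a single grade 4 AE would end the trial and bypass the risk–benefit review that Data monitoring gives to the DSMC.

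**A trigger that leaves out grade 3.** A threshold worded as above grade 3 means grade 4 or higher. Taken at its word, a grade 3 AE prompts no reduction of either drug and does not stand in the way of irinotecan escalation. The escalation consequence falls on the study group only; the regorafenib consequence falls on both arms.

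**Working it through.** The point is textual, and the plan has no figure of its own to reproduce. The rules are set side by side, and the dose consequences follow from the stated steps and caps.

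**Step 1. Related grade 4 AE under each rule**

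| Event | Safety stopping rules | Stopping treatment | Interventions |
|---|---|---|---|
| Hematological, recovers in time | Stop | No stop | Reduce and continue |
| Nonhematological | Stop | Stop | Reduce and continue |

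In the first row the safety stopping rule stands against the other two, whether it refers to the trial or to the patient. In the second row the dose rules and the treatment-stopping rule overlap. They reconcile only if the treatment-stopping rule prevails, which the text does not say.

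**Step 2. The safety stopping rule read at trial level (illustration)**

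Inputs: N = 153 (Sample size estimation) and a per-patient grade 4 rate p. The document gives no p, so the values are assumptions. P(at least one grade 4 AE) = 1 − (1 − p)^153.

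- p = 0.5%: 1 − 0.995^153 = 54%
- p = 1%: 1 − 0.99^153 = 79%
- p = 2%: 1 − 0.98^153 = 95%
- p = 5%: 1 − 0.95^153 = more than 99.9%

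**Step 3. Is a trigger that excludes grade 3 coherent with the rest?**

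The treatment-stopping section refers to grade 3 AEs that have not recovered after two consecutive dose reductions, so it takes for granted that grade 3 leads to reductions. Under the literal trigger it does not. If the treatment-stopping section also prevails for nonhematological grade 4, only hematological grade 4 would ever lead to a reduction. A nonhematological toxicity such as HFSR would trigger nothing at grade 3 and end treatment at grade 4.

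**Step 4. Dose consequences of the literal trigger after a grade 3 AE**

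Next cycle as written, if no escalation is due: dose d. Next cycle with a trigger of grade 3 or greater: d − 30. Next escalation as written: min(d + 30, cap). All in mg/m² irinotecan.

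| Subgroup (cap) | d, as written | d − 30 | Ratio | Next escalation as written |
|---|---|---|---|---|
| 1 (260) and 2 (240) | 180 | 150 | 180/150 = 1.20 | 210 |
| 1 and 2 | 210 | 180 | 210/180 = 1.17 | 240 |
| 1 | 240 | 210 | 240/210 = 1.14 | at most 260 |
| 1, at cap | 260 | 230 | 260/230 = 1.13 (260/240 = 1.08 if back to the previous dose) | none |
| 2, at cap | 240 | 210 | 240/210 = 1.14 | none |
| 3 (180) | 120 | 90 | 120/90 = 1.33 | 150 |
| 3 | 150 | 120 | 150/120 = 1.25 | 180 |
| 3, at cap | 180 | 150 | 180/150 = 1.20 | none |

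Below the cap, the step up becomes available once two cycles at the dose are complete. A patient at 180 could then receive 210 where the reduced dose would be 150, and a subgroup 3 patient at 120 could receive 150 where the reduced dose would be 90.

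Regorafenib after a grade 3 regorafenib-related AE: 120 mg as written, against 120 − 40 = 80 mg.

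**The case against.** **The safety stopping rule may be a loose summary.** It mentions the will and condition of patients, which suggests a patient-level rule, and the treatment-stopping section gives the explicit definition. That is a fair reading and probably the intended one. It does not remove the conflict, because any grade 4 AE still includes the hematological events that the definition leaves out. Nor does condensation into an article explain it: both rules are printed, and they differ.

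**The dose rules and the treatment-stopping rule do not fully agree either.** This stands. They overlap on nonhematological grade 4, so it cannot be said that the safety stopping rule is the only section out of line.

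**The Discussion might seem to settle the intended trigger.** It says "The most frequent grade 3 or higher AE related to regorafenib is HFSR, which results in dose reduction or interruption of treatment". A reader might take this as the trial's own threshold. The sentence carries a citation and reports published experience, so it is not evidence of this protocol's trigger. The evidence of intent is the treatment-stopping section.

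**Larger dose contrasts are tempting.** 210 against 150 is +40%, and 150 against 90 is +67%. As general figures they are too strong: they set a dose reached only after two cycles against a reduction that applies at the next cycle. The two coincide only if the AE falls in the second cycle at that dose. Otherwise the next-cycle contrast is +20% or +33%. The treatment-stopping rule and investigator judgement may also intervene before any step up.

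**A patient count is tempting too.** The Discussion gives grade 3 HFSR rates of "75.0% in the 160-mg group and 16.7% in the 120-mg group", and applying the lower rate to 153 patients would suggest about 26. The rate comes from another study whose group size is not stated, so any interval around that count would rest on an inferred denominator. The document does not support a count.

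**Fig. 1 may state a trigger.** It is not shown, and its legend defines abbreviations for AE, grade and irinotecan. That tempers certainty about how sites apply the threshold, but it would not change the wording repeated in the text for both arms and all three subgroups.

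**The conflict could be resolved the other way.** Stopping for hematological grade 4 would be equally consistent and more cautious. This stands as a clinical choice for the investigators; the statistical point is that the protocol must make one.

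**Conclusion.** Both faults hold on the text.

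A related hematological grade 4 AE that recovers in time receives opposite instructions, and the level at which the safety stopping rule operates is undefined. Read at trial level, it would end the trial on one event, with a probability of 79% at an assumed 1% rate and 95% at 2%. Those rates are illustrations, and the text does not establish that the trial-level reading was meant.

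The dose trigger literally excludes grade 3, against what the treatment-stopping section presumes. Followed as written, the next-cycle irinotecan dose is 8% to 33% higher than under a trigger of grade 3 or greater, depending on subgroup, dose level and the step-back option used. The excess is 20% at the starting dose of subgroups 1 and 2 and 33% at that of subgroup 3. Below the cap, escalation is not blocked. Regorafenib stays 40 mg higher.

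The number of patients affected and the effect on duration of treatment cannot be derived from the document, and no effect on the primary endpoint is claimed. The dose figures assume that sites apply the wording literally, which the document neither confirms nor excludes. The point should be fixed because it concerns operative safety instructions in a trial that is recruiting.

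**What to change.** 1. Reword Safety stopping rules as a patient-level rule that matches the treatment-stopping section (nonhematological grade 4, or failure to recover), and leave termination of the trial to the DSMC review under Data monitoring.
2. State that the treatment-stopping section overrides the dose rules for nonhematological grade 4.
3. In both arms and all three subgroups, change the reduction trigger to *grade 3 or greater*, and allow irinotecan escalation only if no such AE has occurred. Hematological grade 4 then follows the dose actions already written.
4. Have the investigators confirm the thresholds, including whether hematological grade 4 should continue at a lower dose or stop.

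The cost is an amendment during recruitment, approved by the Institutional Review Board and communicated to investigators and registries, as Trial status already requires. It adds no patients, visits or procedures. It may be more than a wording change: if any site has applied the literal trigger, dosing will differ before and after the amendment. The amendment date should therefore be recorded so that the two periods can be told apart in the analysis.

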### Participant timeline

The study is planned to start in May 2018 and is expected to end in May 2020, and will last for 2 years including recruitment, follow-up, data collection and data analysis. The schedule of study visits and assessments is summarized in Table 1.

**Table 1 Tab1:** Schedule of visits and assessments

Assessment/procedure*	Enrollment	Allocation	Clinical regimen		Clinical tumor assessment	Completion/early termination visit	Survival follow-up
Time point	–2 week	0	Every 2 weeks	Every 4 weeks	Every 8 weeks		Every 8 weeks
Eligibility screen	X						
Informed Consent		X					
Randomization		X					
Demographic and medical history	X						
Cancer treatment history	X						
Tumor assessment: carcinoembryonic antigen, and computed tomography or magnetic resonance imaging	X				X	X	X
Eastern Cooperative Oncology Group performance status	X		X			X	
Urinalysis	X		X			X	
Hematology	X		X			X	
Clinical chemistry	X		X			X	
Creatinine clearance (calculated)	X		X				
Physical examination and vital signs	X		X			X	
Weight and height	X		X				
Concomitant medications	X		X			X	
Adverse events	X		X	X	X	X	X
Study drug administration			X	X			
Survival and tumor status/other anticancer treatment							X

*Available data will be collected; no additional diagnostic or monitoring procedures shall be applied to the patients other than routine clinical practice

### Sample size estimation

Using a per-protocol two-sided α of 0.025, a 2:1 randomization between regorafenib plus FOLFIRI dose escalation and regorafenib, and a median PFS of 3.2 months in the regorafenib group [9], the study would have 90% power to detect assumed median PFS of 7.0 months with regorafenib plus FOLFIRI [3]. The assumption of overall probability of events is 0.77 (10 progressions at the end of the study out of 13 in total) [9]. The calculated sample size is 121 patients. Considering a 20% drop-rate, a total of 153 patients should be enrolled into the study, with 102 assigned to the study group (FOLFIRI plus regorafenib group) and 51 to the control group (regorafenib monotherapy group).

### Recruitment

Participants will be enrolled from patients with mCRC whose diseases are refractory to fluoropyrimidines, irinotecan, oxaliplatin, and monoclonal antibodies targeting VEGF, and monoclonal antibodies targeting EGFR for those with *KRAS* wild-type cancers.

### Assignment of interventions

Before study initiation, a randomization sequence is computer generated (GraphPad statistical software, GraphPad, USA) and participants are allocated to either the study group or the control group in a 2:1 ratio in blocks of size 6 by an independent investigator.

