## Methods/design

### Trial design

This is a multicenter, randomized (in a 2:1 ratio) controlled clinical trial with two parallel arms, as summarized in Fig. 1. Neither the investigators nor the patients are masked to treatment allocation. In order to compare the efficacy and safety of regorafenib plus FOLFIRI with dose-adjusted irinotecan based on *UGT1A1* genotype (study group) and regorafenib monotherapy (control group), a total of 153 patients with mCRC that were previously treated with fluoropyrimidines, irinotecan, oxaliplatin, and monoclonal antibodies targeting VEGF, and monoclonal antibodies targeting EGFR for those with *KRAS* wild-type tumors, will be recruited, of which 102 participants will be assigned to the study group and 51 participants will be assigned to the control group in a 2:1 ratio.

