### Study setting

The study will be conducted in four hospital centers in Taiwan.

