### Study participants

Participants will be recruited from Kaohsiung Medical University Hospital, Cathay General Hospital, Taichung Veterans General Hospital and Taipei Veterans General Hospital by the colorectal surgeons. The planned recruitment period is 24 months and informed consent will be obtained from all participants before randomization.

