### Trial status

The trial is currently recruiting; the first patient was recruited on 1 April 2019. Recruitment will be approximately completed before 31 March 2021 and the trial is estimated to end in October 2021. The current protocol is version 1.0, created on 1 February 2019. Any noncompliance with the trial protocol, GCP or manual of procedures requirements will be addressed in study subject source documents and correction actions and/or protocol modifications will be developed and implemented promptly. All protocol modifications will be approved by the Institutional Review Board and communicated to investigators and trial registries.

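### A single, published block size of 6 in an unmasked trial lets recruiters deduce some upcoming allocations; the share ranges from about 1% to 29%, depending on a list structure the article does not state

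*Protocol article*

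**What the plan says.** The section Assignment of interventions (Protocol article) gives the allocation rule in one sentence. First, "Before study initiation, a randomization sequence is computer generated"; patients are then assigned to the two groups "in a 2:1 ratio in blocks of size 6 by an independent investigator". One block size is named. Nothing is said about varying it, about stratifying by centre, or about whether the four hospitals draw on one list or each have their own.

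Three other statements bear on the point:

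- Trial design: "Neither the investigators nor the patients are masked to treatment allocation". Each allocation is visible to the treating team as soon as it is made.
- Study setting and Study participants: "The study will be conducted in four hospital centers in Taiwan", with colorectal surgeons at those hospitals doing the recruiting.
- Trial status: "The trial is currently recruiting; the first patient was recruited on 1 April 2019". Recruitment was expected to run until about the end of March 2021, so the block size became public while patients were still being entered.

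The Exclusion criteria include items that the investigator decides, such as expected poor compliance.

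**The concern.** With a constant and known block size, the end of a block can be worked out from what came before it. Once both control places, or all four study places, have been used, the rest of the block is fixed. In an unmasked trial a recruiter needs only a tally of past allocations to see this.

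The arms differ markedly in burden: an oral drug alone, or the same drug plus repeated infusions with escalating irinotecan. A recruiter who foresees the arm could enter, defer or decline a borderline patient accordingly, and the judgement-based criteria leave room for that. The result would be a prognostic difference between the arms that arises before randomization. Adjustment for measured covariates cannot be relied on to remove it, because the selection may act on features that nobody records. The control arm is planned at only 51 patients, so a modest number of steered entries could matter for progression-free survival.

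The independent investigator keeps the list itself out of recruiters' hands. That does not prevent deduction from a disclosed block size and visible past allocations.

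**Working it through.** **Inputs from the article.** Block size 6 at 2:1, hence 4 study and 2 control per block (Assignment of interventions). Four centres (Study setting). Total 153, planned as 102:51 (Sample size estimation). The article gives no predictability figure to reproduce. Its total follows from its own inputs: 121/0.8 = 151.25, rounded up to 152, and 153 is the next number that divides 2:1.

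**Step 1. Worst case: the recruiter sees every earlier allocation in the block.** An allocation counts as known when only one arm remains in the block.

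- Expected study places left after the last control: 4/(2+1) = 1.333.
- Expected control places left after the last study place: 2/(4+1) = 0.400.
- Sum: 26/15 = 1.733 of 6, or 28.9%. Over 153 patients, 0.289 × 153 ≈ 44.

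Enumerating all 15 orderings of a 4:2 block gives the same total. By position:

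| Position in block | Share of blocks in which it is known |
|---|---|
| 1st, 2nd | 0% |
| 3rd | 6.7% |
| 4th | 20.0% |
| 5th | 46.7% |
| 6th | 100% |

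Most of this certainty concerns the study arm (1.333/6 = 22.2% of allocations). Control is foreseen with certainty for 0.4/6 = 6.7%. A recruiter who always guesses the likelier remaining arm is right 74.4% of the time, against 66.7% from always guessing study.

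**Step 2. One shared list: a site sees only its own patients.** Assume that each patient falls at the site independently with probability p, and that the site knows where blocks begin and end (generous to the recruiter). The site is certain only if both controls, or all four study places, went to its own earlier patients. The two terms of step 1 are then multiplied by p² and p⁴:

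share known at that site = (4/3 · p² + 2/5 · p⁴) / 6

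| Site's share of enrolment, p | Calculation | Known with certainty |
|---|---|---|
| 25% | (0.0833 + 0.0016)/6 | 1.4% |
| 50% | (0.3333 + 0.0250)/6 | 6.0% |
| 70% | (0.6533 + 0.0960)/6 | 12.5% |
| 100% (whole block seen) | (1.3333 + 0.4000)/6 | 28.9% |

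The article gives no split of recruitment by centre, so p is an assumption and the table shows the range.

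**Step 3. Randomly varied block sizes, same worst case as step 1.** Sequences of 153 allocations were simulated. The recruiter sees every earlier allocation and knows which sizes are in use, but not the size of each block.

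| Sizes in use | Known with certainty | Likelier-arm guess correct |
|---|---|---|
| 6 only | about 28% (the last block is incomplete at 153) | about 74% |
| 6 and 9 | about 5% | about 73% |
| 3, 6 and 9 | about 4% | about 74% |

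Varying the sizes removes most of the certainty but hardly changes the accuracy of a best guess, which is dominated by the 2:1 ratio.

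**Step 4. Does a fixed block of 6 secure 102:51?** 153/6 = 25.5, so no. On a single list the last 3 patients come from a half-used block. They contain exactly one control with probability 2 × 6/20 = 0.6, and otherwise none or two (0.2 each).

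**The case against.** The strongest objection is that 29% depends on a condition the article does not state. It speaks of one randomization sequence, in the singular, applied by an independent investigator, and mentions no blocks by centre. On that reading, with four equal centres, the share known is about 1.4%, roughly 2 of 153 patients, and even that credits each site with knowing the block boundaries. List structure and concealment are also details that a journal article commonly leaves to the full protocol. This stands: 29% has to be presented as an upper bound and not as the expected leak.

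It is also fair that most of the certain allocations are to the study arm, already the likelier one, so a best guess gains under 8 percentage points even in the worst case. No effect on the hazard ratio can be derived from the article.

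The objection does not dispose of the point. The constant block size is a stated rule, not an omitted detail, and under any one list structure varying it lowers certain prediction.

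Two stronger readings are tempting and should be resisted. A reader might infer that the scans are read by the same teams who recruit, so that predictability and assessment bias compound; the article says that response is assessed radiologically by RECIST but not who reads the images, and block size does not affect that question anyway. A reader might also infer that centre-stratified randomization is part of the remedy, because centre-adjusted analyses are planned under Statistical methods. It is a separate choice. Within-centre blocks show each recruiter the full history of that centre's list, so moving from one shared list to centre lists could raise predictability.

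**Conclusion.** The point holds in conditional form. The article fixes and publishes one block size in an unmasked, still-recruiting trial that has some discretionary entry criteria, so recruiters can deduce some allocations before entering a patient. The share known with certainty runs from about 1.4% (one shared list, a site enrolling a quarter of patients) through about 6% and 12% (a site enrolling half or 70%) to 28.9%, about 44 of 153 (blocks within centre, or one recruiter seeing the whole list). The shared-list figures assume that sites know the block boundaries, and they apply to the site concerned, not to the whole trial.

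This is an avoidable risk of selection bias. Nothing in the article shows that selection took place, and the point should not be read as saying so. The change is worth making because it is cheap; the trial's validity does not hinge on it.

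**What to change.** For allocations still to be made, replace the fixed block of 6 with block sizes drawn at random from multiples of 3, for example 3, 6 and 9, or 6 and 9. The independent investigator holds the sizes, and they stay out of anything the recruiting sites see. The sentence under Assignment of interventions could say that allocation is 2:1 in permuted blocks of randomly varying size that are not disclosed to recruiters. A mix of 3 and 6 alone is less effective (about 10% known in the worst case), so the larger size should be included.

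The cost is regenerating the unused part of the list and rewording one sentence. Allocations already made are unaffected. The final split may differ slightly from 102:51, but complete blocks of 6 do not guarantee that split now.

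Whether to stratify by centre should be decided on its own merits. If blocks are, or become, centre-specific, varied sizes matter most, because that is where a fixed block of 6 reaches the full 28.9%.
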